### **7.5.2 METHODS FOR MEASUREMENT OF BMR**

On CID 1-3, respiratory measurements of O2 and CO2 will be performed by ventilated hood measurements.

### **7.5.3 PHYSICAL ACTIVITY & 7-D DIET REGISTRATION**

On CID 1-3, physical activity in Subgroup a will be assessed by use of pedometers. During each measurement period subjects will undergo a 7 day recorded food intake, during which time they will wear an activity monitor and assess (once at the end of each day) motivation to eat and mood using a small computerised line-scale system.

### **7.5.4 MEAL TEST**

A meal test will be performed with subjects in Subgroup a on CID 1-2. The subjects will remain semi-recumbent and resting throughout the procedure, and must fast (except for 1 dL of water) until completion of the test.

Information about the meal test procedure will be given out to the subjects. During the meal test subjective appetite ratings will be made using Visual Analogue Scales (VAS).

## **7.6 METHODS OF SAFETY**

NB: The study and study procedures are not expected to result in any adverse effects but if so, these adverse effects are anticipated to be minor. As with any research study, there is a possibility of unforeseeable risks that cannot be anticipated by either the investigators or participants. The study may include risks that are unknown at this time. Physical examinations will be performed before (visit 1 at inclusion) and during the study period if suspicion of side effect or other illnesses are presented.

### **7.6.1 PHYSICAL EXAMINATION**

A brief basic physical examination including questions about medical history, previous drug use, etc. will be performed by a Medical Doctor. The examination results obtained will be recorded as normal/abnormal.

#### **7.6.2 URINE SAMPLE (SPOT)**

Spot urine samples will be taken from every adult subject on CID 1. The urine will be analyzed (by stix) to assess the amount of protein, glucose etc. present.

#### **7.6.3 SUB-STUDY FOR SAFETY ASPECT OF HIGH-PROTEIN DIET IN CHILDREN AND ADULTS**

This specific protocol will assess the potential risks associated with the high protein diet in both children and adults and will examine potential dietary effects on growth and metabolism in children and adolescents. Potential adverse effects on urinary calcium loss, bone loss or renal function will be assessed. The concentrations of serum urea (carbamide), albumin, osteocalcin and creatinine, and urinary albumin, creatinine and U-NTx will be measured in all intervention children on CID 1, 3 and 4. Serum urea and creatinine, and urinary albumin will in addition be measured on CID 2. Serum urea and urinary albumin, creatinine and U-NTx will also be measured in adults on CID 1, 3 and 4. The safety issue will also be addressed at follow-up (week 104) and the general health status of both children and adults will be assessed and certain parameters (e.g. height and weight in children) again measured. Any observed adverse effects (this applies to both children and adults) will be reported to the Ethical Officer in the DiOGenes Project Board ([name] [name], Director of the Institute for Bioethics, Department of Caring Sciences of the University of Maastricht, Netherlands) and action will be taken based on the decisions taken by the Project Board.

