Primary outcome measures for adults are body weight loss maintained (kg), change in body composition, proportion of subjects maintaining > 0, 5 and 10% weight loss, and drop-out rate. Other non-clinical primary measures are to identify biological and psychological traits that determine the family's and individual's responses to the dietary interventions. Secondary end-points are reduction in abdominal obesity, changes in risk factors of type-2 diabetes and CVD and appetite/satiety hormones, and changes in physical activity. Clinical measurements will include in addition the identification and quantification of adipose tissue mRNA and peptide biomarkers. Primary outcome measures for children are changes in the proportion of overweight and obese children at 6 mo, and changes in BMI, and % whole body fat. Secondary end-points for overweight children are reduction in abdominal obesity, changes in waist-hip circumference ratio and blood parameters and changes in physical activity. A sub-study (described below) will assess the effect and safety of the high protein diet in children and adolescents. Dietary effects on bone and kidney health will be assessed and primary safety end-points will include changes in urinary and blood proteins, such as albumin and creatinine.

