#### **7.7.4 BLOOD SAMPLES**

On CID 1-4, blood samples will be taken for analysis of specifically chosen markers that are expected or shown to differ in the dietary regimens (adults).

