#### **7.7.5 24-H URINE SAMPLES**

24-h urinary collection (with PABA control) will be performed from every adult subject on CID 1, visit 11 and 14, CID 3 and 4 to assess urinary nitrogen and other relevant markers such as C-peptide. Subjects will be given written instruction on the 24h urinary sampling procedure.

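### Section 7.6.3 promises to assess urinary calcium loss in children and adults, but no urinary calcium assay is listed for either group; adult renal cover also lacks serum creatinine

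*Protocol*

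**What the plan says.** Protocol section 7.6.3 sets its scope first: "This specific protocol will assess the potential risks associated with the high protein diet in both children and adults". It then names three risks: "Potential adverse effects on urinary calcium loss, bone loss or renal function will be assessed".

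The assays follow, by group and visit:

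- Children, at CID 1, 3 and 4: "The concentrations of serum urea (carbamide), albumin, osteocalcin and creatinine, and urinary albumin, creatinine and U-NTx will be measured in all intervention children".
- The next sentence adds: "Serum urea and creatinine, and urinary albumin will in addition be measured on CID 2".
- Adults: "Serum urea and urinary albumin, creatinine and U-NTx will also be measured in adults on CID 1, 3 and 4".

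The Synopsis (Aims) describes the sub-study in terms of children and adolescents and says that "primary safety end-points will include changes in urinary and blood proteins, such as albumin and creatinine".

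Separately, section 7.7.5, under compliance, has every adult give a 24-h urine with a PABA check at CID 1, 3 and 4 and at two visits in between, "to assess urinary nitrogen and other relevant markers such as C-peptide".

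**The concern.** The aim and the assays stand in the same paragraph and do not match. The aim names urinary calcium loss; the lists that should deliver it contain no calcium.

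This matters because the Background gives unsettled renal and bone effects of high-protein diets as part of the case for the trial, and asks for clarification in children above all. The section on participation of children justifies their blood sampling by the need to address the safety of the diet. An ethics committee or a parent reading 7.6.3 would expect a result on calcium loss.

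A statistical analysis plan cannot repair the gap. Which analytes are run, on which specimen and at which visit, is for the protocol to fix, and an analyte that was never measured cannot be analysed.

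**Working it through.** No arithmetic beyond counting applies. The check sets the named risks against the listed assays, then looks for the missing ones elsewhere.

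**Step 1. Risks against assays in 7.6.3.**

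| Named risk | Children | Adults |
|---|---|---|
| Urinary calcium loss | none listed | none listed |
| Bone loss | U-NTx, osteocalcin; DEXA bone mineral content where DEXA is done (7.2.3) | U-NTx; DEXA bone mineral content where DEXA is done (7.2.3) |
| Renal function | serum urea and creatinine; urinary albumin and creatinine | serum urea; urinary albumin and creatinine; no serum creatinine |

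Three risks in two groups make 3 × 2 = 6 cells. Two have no listed assay (calcium, both groups), one is partial (adult renal function) and three are covered. U-NTx and osteocalcin are bone-turnover markers and do not measure calcium excretion, so they do not fill the calcium row.

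**Step 2. Could calcium be covered elsewhere?**

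- 7.3.3 allows other relevant markers in adults and children, but in fasting blood, so it cannot supply a urinary measure.
- 7.6.2 is an adult dipstick test at CID 1 only; protein and glucose are the examples given.
- 7.7.4 concerns unspecified adult blood markers for compliance.
- 7.7.5 has open wording on urine, but for adults only, under compliance, with nitrogen and C-peptide as the named analytes.

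Calcium is therefore named only in the sentence stating the aim. For adults the open wording of 7.7.5 could admit it without committing to it. For children no comparable wording on urinary markers exists.

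**Step 3. Is the creatinine in the adult sentence serum or urinary?** The adult sentence puts creatinine after the word urinary, between albumin and U-NTx. The children's sentence names creatinine twice, once in the serum group and once in the urinary group, so the protocol separates the two when it means both. The natural reading is that adult creatinine is urinary only.

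The CID 2 sentence follows the children's list and precedes the adult one, so it most naturally concerns children. If it were read to include adults, it would give them one serum creatinine, at week 0, before the intervention diets start. No change could be calculated from that.

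Counts of visits with a named serum creatinine:

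- Children: CID 1, 3 and 4 plus CID 2 = 4 visits.
- Adults: 0 of the 3 visits in their list.

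**Step 4. What the adult gap costs.** Creatinine clearance is (urinary creatinine concentration × urine volume) / (serum creatinine × collection time). An estimated filtration rate based on creatinine also needs the serum value. Without it neither can be computed. Urinary albumin, its ratio to urinary creatinine, and serum urea remain available at CID 1, 3 and 4. The Synopsis (Subjects) aims for 110 adults at randomisation.

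**The case against.** The strongest defence has three parts.

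**The list need not be exhaustive.** The Synopsis introduces its safety end-points as examples, and 7.3.3, 7.7.4 and 7.7.5 leave room for further markers. This stands to the extent that the right description is *not listed* rather than *certain not to be measured*. It does not supply a commitment: none of these clauses names calcium or adult serum creatinine, two of them concern compliance, and none offers a urinary marker in children.

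**A shorter adult renal panel is a legitimate choice.** This largely stands. The protocol never promises a clearance or a filtration rate, and the Synopsis ties its albumin and creatinine end-points to children and adolescents, who have both in serum and urine. A reader might infer that two of the three named risks cannot be assessed. The documents do not support that: children have a full set of renal markers, and adults have urinary albumin, urinary creatinine and serum urea at three visits. The adult panel is incomplete, not empty.

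**Urea.** A reader might also infer that adult serum urea would be uninterpretable, because the diets differ in protein by design and urea could follow intake. The protocol says nothing on how serum urea responds to diet, so that argument would rest on outside knowledge and is not made here. Urinary albumin is measured at the same adult visits in any case.

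**Conclusion.** The point holds in a limited form. Urinary calcium loss is a stated safety aim for both groups with no listed measurement in either: one named risk of three. Adult renal function is partly covered; what is missing is a named serum creatinine, and with it any creatinine-based estimate of filtration.

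This should be corrected, but it does not threaten the trial. Randomisation, the primary outcome and its analysis are untouched, and bone loss and children's renal function are covered.

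The conclusion assumes that 7.6.3 is followed as written, that the adult creatinine is urinary, and that the open wording elsewhere is not being used to add calcium or adult serum creatinine without saying so.

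**What to change.** In 7.6.3, do one of the following for calcium:

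- Add urinary calcium to the urine assays at CID 1, 3 and 4. For adults, use the 24-h collections already made at those visits under 7.7.5. For children, report a calcium/creatinine ratio in the safety urine, where urinary creatinine is already listed.
- Or delete urinary calcium loss from the stated assessment.

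Also add serum creatinine to the adult assays at CID 1, 3 and 4, on the fasting blood already drawn, so that adults match children on this marker. If a clearance is wanted, state that adult urinary creatinine is measured in the 24-h collection: 7.6.3 does not name the specimen, and 7.7.5 does not list creatinine.

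One check when amending: Section 3 and 7.6.3 provide for children's urine, but the children's visit lists in 7.1.2 show only blood samples at the CIDs. The urine should appear there too.

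The cost is a small added laboratory expense, for which the documents give no figure, and a short amendment. No new visit or procedure is needed. Taking the deletion route costs nothing in the laboratory, but gives up a safety question that the protocol set itself.

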### **Ethics**

The study will be performed according to the latest version of the Declaration of Helsinki, the UN Convention on the Rights of the Child and the Current International Conference on Harmonization

---

 CID 2 for children will take place in week 4

(ICH) guidelines. Wherever possible, the study will be performed according to the current Good Clinical Practice (GCP) guidelines. An application will be submitted to the regional Ethics Committee and the study will not be undertaken without a positive statement from the committee regarding the study. All subjects (including children where possible) must give verbal and written informed consent before they can be entered into the study.

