In week 4 of period 1, the children will visit the Department for their CID 2. This will include (all children) anthropometric measurements and blood sample/urine collection, with additional measures of body composition (DEXA/bioimpedance) for overweight children only.

Before entering intervention period 2, adults and children visit the Department for CID 3, including (adults) anthropometric measurements, BP, blood sample and 24-h urine collection, fat biopsy, OGTT and analysis of body composition (DEXA scan). Measures for children include (all children) anthropometric measurements and blood sample/urine collection, with additional measures of body composition (DEXA/bioimpedance) for overweight children only.

Subgroup a will complete a 7-day food record and undergo BMR and DLW measurements, and have physical activity measured by use of a pedometer.

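### At week 4 the children's urinary albumin is listed without urinary creatinine, so unless the sample is timed that one value cannot be corrected for urine dilution

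*Protocol*

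**What the plan says.** Section 7.6.3 sets out the laboratory safety markers for the high-protein sub-study. After the serum markers, it states that "urinary albumin, creatinine and U-NTx will be measured in all intervention children on CID 1, 3 and 4". The next sentence adds a shorter set for one more visit: "Serum urea and creatinine, and urinary albumin will in addition be measured on CID 2". The section describes the measurements as concentrations: "The concentrations of serum urea (carbamide), albumin, osteocalcin and creatinine" opens the list that also covers the urinary markers.

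For children, CID 2 is not the week-0 visit that adults have. Footnote 1 of the Synopsis says "CID 2 for children will take place in week 4", and Section 3 (intervention period 1) agrees: "In week 4 of period 1, the children will visit the Department for their CID 2". Section 3 also plans urine at that visit: "This will include (all children) anthropometric measurements and blood sample/urine collection". No duration, timing or volume is given.

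For adults the sample type is explicit. Section 7.7.5 says "24-h urinary collection (with PABA control) will be performed from every adult subject", and Section 7.6.2 adds a spot sample at CID 1. The Synopsis (Aims) counts changes in urinary and blood proteins among the primary safety end-points and gives albumin and creatinine as examples. It attaches no time point to them.

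**The concern.** The protocol chose to measure urinary albumin in children soon after the diet starts, and that value should be interpretable. In an untimed sample, albumin concentration depends on how much albumin is excreted and on how dilute the urine is. Urinary creatinine measured in the same sample is the correction that the protocol makes possible at CID 1, 3 and 4. At week 4 it is not listed, so a laboratory following Section 7.6.3 would not run it.

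At stake is the early reading of one marker from the named primary safety end-points, in the group whose safety on a high-protein diet the Background singles out as needing clarification. A creatinine-corrected change from CID 1 to week 4 could not be calculated, and the analysis cannot recover an assay that was never run.

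**Working it through.** The protocol states no figure to reproduce. The check is to lay out the markers by visit and then ask whether another correction is available.

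**Step 1. Children's markers by visit (Section 7.6.3)**

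| Marker | CID 1 (before the adults' LCD) | CID 2 (week 4) | CID 3 (week 26) | CID 4 (week 52) |
|---|---|---|---|---|
| Serum urea | yes | yes | yes | yes |
| Serum creatinine | yes | yes | yes | yes |
| Urinary albumin | yes | yes | yes | yes |
| Urinary creatinine | yes | **not listed** | yes | yes |
| Albumin/creatinine ratio possible | yes | **no** | yes | yes |

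The creatinine in the CID 2 sentence belongs to serum: it is joined to serum urea, and the urinary marker follows after a comma under its own adjective. The sentence before it lists creatinine twice, once among the serum markers and once among the urinary ones, so the protocol keeps the two apart. The ratio can be formed at 3 of 4 visits.

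**Step 2. Is week 4 the only laboratory point in the interval?** The children's visit lists for weeks 2, 6, 10, 14, 18 and 22 (Sections 7.1.2.4 and 7.1.2.6 to 7.1.2.8) contain weight, height, dietary instruction, adverse events and concomitant medication, but no blood or urine. The next sampling is week 26. Urinary albumin at week 4 is therefore the only urinary renal marker in children between the start of the diet and week 26.

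**Step 3. Does the protocol supply another correction?** A timed collection with recorded volume would give an excretion rate, and creatinine would not be needed. The protocol specifies 24-hour collection for adults (Sections 3 and 7.7.5) and never for children. It does not call the children's sample a spot sample either; the only spot sample described is for adults (Section 7.6.2). That the children's sample is untimed is an inference from the adults-only 24-hour text and from the word concentrations. It is well supported but not stated.

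**Step 4. What dilution does to an untimed value.** Let E be the albumin excretion rate and V the urine flow. The concentration is C = E / V. If excretion changes by a factor e and flow by a factor f, the measured concentration changes by e / f. The protocol gives no flow figures, so the values below are assumptions that show the range.

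- e = 1, f = 1.2: 1 / 1.2 = 0.83, a fall of 17%
- e = 1, f = 1.5: 1 / 1.5 = 0.67, a fall of 33%
- e = 1, f = 2.0: 1 / 2.0 = 0.50, a fall of 50%
- e = 1, f = 0.5: 1 / 0.5 = 2.0, a spurious doubling
- e = 1.5, f = 1.5: 1.5 / 1.5 = 1.0, no visible change although excretion has risen by 50%

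With creatinine in the same sample, the ratio is (E_albumin / V) / (E_creatinine / V) = E_albumin / E_creatinine. Flow cancels. The ratio then rests on creatinine excretion being comparable, which would apply equally at CID 1, 3 and 4.

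**Step 5. Noise or bias?** If flow varies between children but not systematically by diet, the extra variation widens the week-4 comparison without shifting it. If flow differs by diet, the between-arm comparison of concentrations is shifted, in either direction. The protocol does not say which applies.

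**Step 6. Is a urine sample scheduled?** Section 3 names urine for all children at CID 1, 2, 3 and 4. The children's visit lists for the same four visits (Sections 7.1.2.2, 7.1.2.5, 7.1.2.9 and 7.1.2.11) name fasting blood and no urine. Staff working from the visit lists alone would collect none.

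**The case against.** The strongest reply is that little depends on the week-4 value. Section 8.2.4 and the primary hypothesis place the comparisons at weeks 26 and 52, and Section 8.2.6 places those for secondary variables at week 26. Urinary creatinine is available at both visits. No test, threshold or decision rule uses week-4 albumin. This stands, and it is why the point is small.

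A reader might infer that early renal monitoring in the children is missing. It is not: serum urea and serum creatinine are measured at week 4, and adverse events are recorded at the family meetings between week 0 and week 26.

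A reader might also infer that week-4 albumin cannot be compared with anything. Raw concentration is measured at all four visits and can be compared across visits and between randomised arms. Only the dilution-corrected comparison is lost.

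A third tempting step is that an early rise on the high-protein diets would be hidden. That requires urine flow to rise on those diets by about as much as excretion, and nothing in the protocol says that it would.

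Finally, the children's sample might be timed. The protocol does not exclude this. If it is timed with recorded volume, the remedy is one sentence saying so.

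The reply that this can wait for the statistical analysis plan does not stand for the assay itself, because an analysis plan cannot form a ratio from a measurement that is not made. It does stand for the choice of reported measure.

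**Conclusion.** The concern holds in limited form. Section 7.6.3 lists urinary albumin without urinary creatinine at the children's CID 2, so a creatinine-corrected value is available at three of the four visits and not at the only laboratory safety sampling between the start of the diet and week 26. This assumes that the children's sample is untimed, which the text supports but does not state. On that assumption the week-4 concentration carries noise from dilution, plus bias if flow differs by diet. The percentages above show the scale under assumed flow changes and are not estimates for this trial. The documents do not support saying that the marker is useless, that early renal safety goes unmonitored, or that harm would be masked. It is a small, inexpensive gap in an assay list, worth closing because the marker belongs to the primary safety end-points.

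**What to change.** In Section 7.6.3, add urinary creatinine to the children's CID 2 list, assayed in the same sample as the albumin, so that an albumin/creatinine ratio can be formed at CID 1 to 4. If the children's urine is in fact a timed collection with recorded volume, say so there instead. Whether the ratio becomes the reported measure at every visit can be left to the statistical analysis plan.

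Also add the urine sample to the children's visit lists for CID 1 to 4 (Sections 7.1.2.2, 7.1.2.5, 7.1.2.9 and 7.1.2.11), so that they agree with Section 3.

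The cost is one extra routine assay per child at one visit, on urine that Section 3 already plans to collect. No visit or sample is added to the Section 3 plan.
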